##### Secondary outcome analyses

We will conduct four exploratory secondary outcome analyses, one each for depression, anxiety, anger, and trauma, designed to leverage the longitudinal nature of outcome assessment in this study. The first will consist of a LMM in which IDS-C will be compared across study arms at each follow-up visit (three fixed effects), controlling for gender, baseline IDS-C scores, and baseline receipt of psychotherapy. Here we will include random effects for group participation and individual, as we will need to account for within-person correlation. We will consider a simpler model for parsimony including follow-up visit as a continuous variable, as in a linear growth mixed effects model, and select the model that minimizes the Bayesian Information Criterion. The visit-specific coefficients on study arm will address the question: “for two patients with the same baseline depressive symptoms, gender, and baseline receipt of psychotherapy, if one is given the M-Body intervention and the other enhanced usual care, will the patients have different depressive symptoms after 2, 4, and/or 6 months?” The secondary outcome analyses for GAD and anger will use similar models to those described here for IDS-C, this time additionally including baseline GAD or anger scores as appropriate. The secondary outcome analysis for trauma will consist of a linear mixed model (LMM) in which mean 6-month trauma will be compared across study arms (fixed effect), controlling for gender, baseline IDS-C scores, and baseline receipt of psychotherapy, with a random group effect. If issues with model convergence are encountered, we will consider simpler models, such as a linear model with fixed effects for groups, or a linear model with no group effects specified. No interim analysis is planned or will take place; we do not anticipate study developments to require interim analyses.

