## Methods

### Overview

Adults who demonstrate a minimum threshold of depressive symptoms will be randomly assigned to either an eight-session mindfulness group intervention or enhanced usual care (“control”). Participants will be followed for 6 months after randomization, with assessments at baseline and 2, 4, and 6 months post-baseline (Table 1). During an in-person visit at baseline, a trained research assistant will administer the clinical instruments, collect stress-related biomarker data, and oversee the completion of the self-report surveys. At follow-up, participants will complete self-report surveys and stress-related biomarker data collection during an in-person visit and an independent evaluator (trained research assistant) will contact them by phone to assess the primary outcome. The primary outcome will be depressive symptoms at 6 months post-baseline. To take advantage of the repeated outcome assessments, secondary outcomes will compare 2-, 4-, and 6-month measurements of depression, anxiety, trauma symptoms, and anger. Northwestern University’s Institutional Review Board (IRB) and the research committee of the FQHC approved the study protocol.

**Table 1 Tab1:** Description of all interactions between participants and M-BODY personnel

Assessment location	Study timeline^a^	M-BODY personnel	Measurements	Time (minutes)
In-person^b^ or phone	Pre-baseline (screening)	Research assistant or study coordinator Study phlebotomist	PHQ-9	10
In-person^b^	Baseline	Research assistant or study coordinator Study phlebotomist	MINI Self-report surveys^d^ Dried blood spot Body Mass Index Blood pressure	90
In-person^b^	2 months	Research assistant or study coordinator Study phlebotomist	Self-report surveys^d^ Dried blood spot Body Mass Index Blood pressure	90
Phone	2 months	Independent evaluator^c^	IDS-C LIFE^e^	15
In-person^b^	4 months	Research assistant or study coordinator Study phlebotomist	Self-report surveys^d^ Dried blood spot Body mass index Blood pressure	90
Phone	4 months	Independent evaluator^c^	IDS-C LIFE^e^	15
In-person^b^	6 months	Research assistant or study coordinator Study phlebotomist	Self-report surveys^d^ Dried blood spot Body Mass Index Blood pressure	90
Phone	6 months	Independent evaluator^c^	IDS-C LIFE^e^	35-45

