### Measures

For a brief overview of all measures and assessment times, see Table 3.

**Table 3 Tab3:** Instruments used to collect data during the M-Body study

			Scoring			Visit administered^a^				
Instrument	Construct(s) measured	Reliability/validity^b^	No. items	Score range	Interpretation	T0	T1	T2	T3	T4
*Primary outcome*										
Structured interview guide for the inventory of depressive symptomology (Clinician-rated) Rush et al., 1986 [62]	Depressive symptoms	High/moderate Rush et al., 1986 [62]	30	0–84	0–13 = None 14–25 = Mild 26–38 = Moderate 39–48 = Severe 49–84 = Very Severe		x	x	x	x
*Secondary outcomes*										
Generalized anxiety disorder - 7-item scale Spitzer et al., 2006 [66]	Generalized anxiety	High Spitzer et al., 2006 [66]	7	0–28	5 = Mild 10 = Moderate 15 = Severe ≥10 indicates probable GAD diagnosis		x	x	x	x
Anger self-report questionnaire Reynolds et al., 1994 [67]	Anger	High/moderate Reynolds et al., 1994 [67]	30	30–180	Higher scores indicate increased trait anger		x	x	x	x
Posttraumatic stress disorder (PTSD) for DSM-5 (PCL-5) Weathers, et al., 2013 [68]	Trauma; PTSD symptom severity	High Blevins et al., 2015 [69]	20	0–80	≥31 indicates probable PTSD diagnosis		x			x
*Other psychological assessments*										
Patient Health Questionnaire-9-item Kroenke et al., 2001 [70]	Depression	High Kroenke et al., 2001 [70]	9	0–27	1–4 = Minimal 5–9 = Mild 10–14 = Moderate 15–19 = Moderately severe 20–27 = Severe	x				
Mini International Neuropsychiatric Interview Sheehan et al., 1998 [71]	Major depressive episode(s), Dysthymia, Generalized Anxiety Disorder	High Sheehan et al., 1998 [71]	46	N/A	N/A		x			
Longitudinal Interval Follow-up Evaluation – II (Modified) Keller et al., 1987 [72]	Major Depressive Episode(s), Dysthymia, Generalized Anxiety Disorder	High Keller et al., 1987 [72]	22	0–48	A coding of 5 and above indicate meeting DSM-IV criteria.			x	x	x
HIV cost and services utilization study baseline questionnaire, module 6: utilization of care—modified Shapiro et al., 1999 [73]	Mental health providers, social support, usual source of medical care, utilization of care and services used	N/A	44	N/A	N/A		x	x	x	x
Social problems questionnaire (Modified) Corney and Clare 1985 [74]	Social problems, difficulties and dissatisfactions	N/A	28	0–112	Higher scores indicate greater social difficulties		x			

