Implementation Leadership Scale (Modified) Aarons et al., 2014 [84]	Implementation leadership	High Aarons et al., 2014 [84]	7	0–48			x	x	x	x
Evidence-Based Practice Attitude Scale Aarons, 2004 [85]	Attitudes toward adoption of evidence-based practices	High Aarons, 2004 [85]	15	0–60			x			
Clinical Effectiveness and Evidence-Based Practice Questionnaire (Modified) Upton and Lewis, 1998 [86]	Professional’s attitudes toward concepts and application of evidence-based practice and clinical effectiveness	High Upton and Lewis, 1998 [86]	3	0–24			x	x	x	x

*Abbreviations: No.* number of, *HIV* human immunodeficiency virus, *DSM-5* Diagnostic and Statistical Manual of Mental Disorders, 5^th^ Edition, *DSM-IV* Diagnostic and Statistical Manual of Mental Disorders, 4^th^ Edition

^a^The visit abbreviations “T0,” “T1,” “T2,” “T3,” and “T4” correspond to screening, baseline, and 2-, 4-, and 6-month follow-ups

^b^Low (*α* < 0.60, *κ* < 0.41, ICC < 0.50, *r* < 0.35), moderate (0.60 < *α* < 0.70, 0.41 < *κ* < 0.60, 0.50 < ICC < 0.75, 0.36 < *r* < 0.67), high (*α* > 0.70, *κ* > 0.60, 0.75 > ICC > 0.90, *r* > 0.90) (100, 101, 102, 103)

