#### Secondary outcomes

Major depressive disorder and persistent depressive disorder will also be assessed as a secondary outcome using The Mini International Neuropsychiatric Interview (MINI 6.0) at *baseline* [71]. The MINI is a short clinician-administered diagnostic interview that assesses current and lifetime psychiatric disorders based on the American Psychiatric Association’s Diagnostic and Statistical Manual of Mental Disorders – 4^th^ edition (DSM-IV) and International Classification of Diseases (ICD-10) [71]. Study team members administering the MINI were trained by an expert clinician and rated mock interviews until they reached acceptable reliability with the expert clinician.

Longitudinal measures of depressive symptoms, generalized anxiety, anger, and trauma symptoms will also be secondary outcomes (Table 3). Generalized anxiety will be measured using the Generalized Anxiety Disorder-7 Scale (GAD-7) [66]. The GAD-7 is a 7-item self-report measure of generalized anxiety symptoms. Scores of 10 or greater are predictive of a likely GAD diagnosis. Anger will be measured using the Anger Self-Report Questionnaire, which is a single-factor, 30-item self-report measure of anger [67]. Both anxiety and anger will be assessed by self-report at baseline and 2, 4, and 6 months. Post-traumatic stress will be measured using the PTSD Checklist for DSM-5 (PCL-5) [68]. The PCL-5 is a 20-item self-report measure of PTSD symptom severity, administered at baseline and 6 months.

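### The 6-month trauma model omits baseline PCL-5, which is collected, while the other three secondary models include the outcome's own baseline

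*Protocol article*

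**What the plan says.** Under Secondary outcome analyses, the article sets out four exploratory analyses: depression, anxiety, anger and trauma.

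- **Depression:** the IDS-C model adjusts for gender, baseline IDS-C and baseline psychotherapy, so it contains its own baseline.
- **Anxiety and anger:** similar models, "this time additionally including baseline GAD or anger scores as appropriate".
- **Trauma:** a single-time-point linear mixed model "in which mean 6-month trauma will be compared across study arms (fixed effect), controlling for gender, baseline IDS-C scores, and baseline receipt of psychotherapy", plus a random group effect.

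Under Secondary outcomes, the measurement schedule is explicit: "The PCL-5 is a 20-item self-report measure of PTSD symptom severity, administered at baseline and 6 months". In Table 3 the PCL-5 row carries two visit marks, against four for GAD-7 and anger, which agrees with that sentence.

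The Methods Overview says something different about timing: "secondary outcomes will compare 2-, 4-, and 6-month measurements of depression, anxiety, trauma symptoms, and anger". Secondary outcomes also groups trauma with the longitudinal measures, and Secondary outcome analyses describes all four analyses as "designed to leverage the longitudinal nature of outcome assessment in this study".

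**The concern.** The trauma covariate list is written out in full, so this is not a detail left open for a separate analysis plan. It departs from the rule applied to the three sister outcomes, and no reason is given. Stratification does not supply one. Initial IDS-C severity is a stratification factor, which justifies keeping IDS-C in the model, but the anxiety and anger models keep it and still add their own baselines.

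The outcome's own baseline usually carries prognostic information that a score on another construct captures only in part. Leaving it out gives up precision. It also leaves any chance difference between arms in baseline PTSD symptoms corrected only as far as baseline IDS-C happens to track it. Randomization is not stratified on PCL-5, so the model is the only place to correct the rest.

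**Working it through.** **1. The plan's own figure, as context.** The Sample size section claims 80% power at d = 0.4 for secondary outcomes with 192 women, that is 96 per arm, at a two-sided 5% level. Without covariates or clustering:

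power = Φ(d/√(2/n) − 1.96) = Φ(0.4/0.1443 − 1.96) = Φ(0.811) = 0.791.

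With a design effect of 1 + 11 × ICC in both arms, power is 0.787 at ICC 0.001 and 0.749 at ICC 0.01. The 80% therefore reproduces closely at the low end of the stated ICC range. It assumes no covariate adjustment.

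**2. What adding baseline PCL-5 does.** The documents give no PCL-5 standard deviation and no correlations, so the three inputs below are assumptions:

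- r: baseline PCL-5 with 6-month PCL-5
- a: baseline IDS-C with 6-month PCL-5
- c: baseline IDS-C with baseline PCL-5

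Residual variance, as a fraction of the 6-month PCL-5 variance:

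- IDS-C only: 1 − a²
- IDS-C and PCL-5: 1 − (a² + r² − 2arc)/(1 − c²)

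The difference between the two is (r − ac)²/(1 − c²). Equivalent extra participants = (IDS-C only)/(both) − 1.

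| r | a | c | IDS-C only | Both | Cut | Equivalent extra participants |
|---|---|---|---|---|---|---|
| 0.5 | 0.35 | 0.6 | 0.878 | 0.746 | 15% | 18% |
| 0.6 | 0.40 | 0.6 | 0.840 | 0.638 | 24% | 32% |
| 0.7 | 0.45 | 0.6 | 0.798 | 0.509 | 36% | 57% |
| 0.4 | 0.50 | 0.7 | 0.750 | 0.745 | about 1% | about 1% |
| 0.7 | 0.30 | 0.5 | 0.910 | 0.507 | 44% | 80% |

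The first three rows are the central sets. The last two are the extremes of a wider grid: r from 0.4 to 0.7, with (a, c) at (0.3, 0.5), (0.4, 0.6) and (0.5, 0.7). The middle row worked through: (0.16 + 0.36 − 2 × 0.40 × 0.6 × 0.6)/(1 − 0.36) = 0.232/0.64 = 0.3625, so the residual is 0.6375 and 0.84/0.6375 = 1.32.

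**3. In terms of power.** At 96 per arm, d = 0.4 and no design effect, power over the wider grid is 0.83 to 0.89 with IDS-C alone and 0.86 to 0.97 with both. In the middle row it goes from 0.856 to 0.935. The smallest gain is 0.893 to 0.894 and the largest is 0.828 to 0.973.

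**4. Chance imbalance, middle row.** The standard error of the arm difference in baseline PCL-5 is √(2/96) = 0.144 SD. The part not explained by baseline IDS-C is 0.144 × √(1 − 0.36) = 0.115 SD. The coefficient of baseline PCL-5 given IDS-C is (0.6 − 0.24)/0.64 = 0.5625. The resulting 95% range in the estimated effect is ±1.96 × 0.5625 × 0.115 = ±0.13 SD. This is the same quantity as the extra variance in step 2 seen another way, and it is already inside the standard error.

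**5. Visit schedule, side by side.** The Overview puts trauma at 2, 4 and 6 months. The Secondary outcomes text puts PCL-5 at baseline and 6 months. Table 3 gives it two marks, and its visit codes "correspond to screening, baseline, and 2-, 4-, and 6-month follow-ups". The other trauma instruments in Table 3 (LEC-5 and Criterion A) also carry two marks, so no trauma measure is scheduled at 2 or 4 months. The specified trauma model is at 6 months only and agrees with the schedule.

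**The case against.** The strongest reply is that little harm follows. Omitting a prognostic covariate from a linear model in a randomized trial does not bias the arm effect, and the standard error already allows for chance imbalance. Both statements are correct. A reader might infer that any baseline PCL-5 imbalance passes straight into the estimate. That goes too far, because baseline IDS-C absorbs part of it and randomization is stratified on IDS-C severity.

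The second reply is that the gain is assumed. That also stands. With r = 0.4, a = 0.5 and c = 0.7, baseline PCL-5 adds almost nothing, so no single percentage can be presented as established. The calculation also leaves out gender, psychotherapy and the group effect. Nor does the omission threaten the plan's own target: under the assumed correlations, and without a design effect, IDS-C adjustment alone gives at least 0.83 at d = 0.4.

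The third reply concerns timing. A reader might infer from the Overview that 2- and 4-month trauma analyses are planned and cannot be delivered. The documents do not support that. The analysis section specifies no such analysis, and the schedule and the model agree with each other. What remains is a loose sentence in a summary.

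None of this supplies a reason for treating trauma differently from the other three outcomes.

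**Conclusion.** The omission is real: trauma is the only one of the four secondary outcomes whose stated covariates exclude its own baseline, although that baseline is collected. The effect is lost precision and incomplete correction of chance imbalance on an exploratory outcome. There is no systematic bias, and the primary outcome is unaffected.

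The text settles the omission. Its size is uncertain: the cut in residual variance is 15% to 36% under the central assumptions and about 1% to 44% over the wider range, all resting on correlations that the documents do not give. It is a modest point, worth acting on because the data are already being collected.

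The visit discrepancy in the Overview is a separate wording correction and adds no weight to the main point.

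**What to change.** Add baseline PCL-5 as a covariate in the 6-month trauma model and keep gender, baseline IDS-C, baseline psychotherapy and the random group effect. Record the change before any arm comparison of PCL-5 is seen. The Randomization section says the statistical analysis team is not blinded, so a covariate added later would look like a discretionary choice.

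In the Methods Overview, limit the 2- and 4-month comparisons to depression, anxiety and anger, and state that trauma is compared at 6 months. The longitudinal label in Secondary outcomes and Secondary outcome analyses should be qualified in the same way.

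The cost is one covariate and a few words of text. No new data collection is needed, because baseline surveys are completed before randomization.

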### Statistical plans

#### Sample size

Our sample size was chosen to ensure adequate power to detect significant differences in the primary study outcome, IDS-C, between the intervention arm and enhanced usual care. We plan to enroll both sexes, but we anticipate 85% of participants to be female; thus, power considerations are stratified by sex. The project will enroll 274 adults (226 women, 48 men; ages 18–65 years) who meet previously described eligibility criteria.

To determine study sample size, we assumed a two-sided 5% type-I error rate, standard deviation of up to 14 units for the IDS-C (according to preliminary data on the IDS-self report), and a meaningful difference across arms of six points on average on the IDS-C [58]. Analyses will use linear mixed effects models with random effects for blocks and fixed effects for treatment assignment. Since participants will be enrolled in groups of approximately 15 at a time and intervention will be delivered in a group setting, there is a possibility of an intra-cluster correlation (ICC). Previous literature has suggested that ICC tends to be low in group intervention studies, so here we considered ICC values 0.001–0.01 [91]. Under these assumptions, eight groups of women per arm (each of size 12; i.e., 96 women per arm) or 192 women total would ensure 84% power to detect a meaningful difference across arms. To combat anticipated 15% study attrition, we plan to enroll 226 women [59]. Power analyses were conducted via simulation in the R programming language (version 4.1.1) and verified using PASS (version 15) [92]. Note that our initial design and power analyses involved cluster randomization rather than block randomization. Because cluster randomized trials tend to have lower power, our original power analyses suggested 240 women would be required for 80% power, and thus, opting for block randomization reduces the number of participants required.

Additionally, we plan to enroll two groups of men, each of size approximately 12 (i.e., 48 men). We do not anticipate that we will have adequate power to detect meaningful differences across arms in men, and thus, analyses in men will be hypothesis-generating and assess feasibility in this population.

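### In the exploratory longitudinal analyses, the minimum-BIC rule can replace the promised visit-specific arm effects with a straight line, and the convergence fallback does not say that within-person correlation is kept

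*Protocol article*

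**What the plan says.** Under Secondary outcome analyses, the protocol describes the longitudinal depression model thus: "The first will consist of a LMM in which IDS-C will be compared across study arms at each follow-up visit (three fixed effects"). It adds: "Here we will include random effects for group participation and individual, as we will need to account for within-person correlation". GAD-7 and anger use similar models. Trauma has one follow-up measurement, at 6 months, with a random group effect only.

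The section then considers visit as a continuous variable, for parsimony, and will "select the model that minimizes the Bayesian Information Criterion". The next sentence returns to the visit-level target: "The visit-specific coefficients on study arm will address the question" of whether the arms differ after 2, 4 and/or 6 months.

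After the trauma model comes the fallback: "If issues with model convergence are encountered, we will consider simpler models". Two examples of what might then be fitted follow in that sentence: "such as a linear model with fixed effects for groups, or a linear model with no group effects specified". The section calls all four analyses exploratory. The primary model, under Primary outcome analyses, is a separate single-time comparison with no BIC step.

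**The concern.** Two sentences in this section pull against each other. One says visit-specific coefficients answer the question. The other lets a data-driven criterion remove them. With three visits, the linear model saves only two parameters: one for curvature in the control trajectory and one for curvature in the arm difference. BIC charges ln(N) for each, so it tends to keep the line unless the departure is large. An early gain that partly fades, or a delayed gain that plateaus, is what a three-visit comparison should show, and a line smooths it away.

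The fallback raises a smaller issue. Read literally, a linear model has no person effect, although the section includes one "as we will need to account for within-person correlation". If the fallback were applied to the three-visit outcomes, three rows from one person would be treated as independent.

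**Working it through.** **The plan's own figure.** Sample size gives 96 women per arm, SD 14, a 6-point difference and two-sided 5%. SE = 14 × √(2/96) = 2.02. Power = Φ(6/2.02 − 1.96) = 84.4%, which matches the stated 84%. Enrolment 192/0.85 = 225.9, so 226, also matches. The document states no figure for the secondary models.

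**Inputs for the check.** From the protocol: 96 per arm, SD 14, classes of 12, three follow-up visits, and for the ICC, "so here we considered ICC values 0.001–0.01". Assumed, because the protocol gives no value: within-person correlation ρ of 0.4–0.6 (up to 0.7 for the standard errors), a flat control trajectory, and the shapes of the effect. Negative values favour M-Body.

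**What a line does to a non-linear effect.** For true arm effects (a, b, c) at equally spaced visits, let d = a − 2b + c. With a random person intercept and complete data, the fitted line misses the truth by d/6 at months 2 and 6 and by d/3, in the opposite direction, at month 4.

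- −6/−3/−3: d = −3, line −5.5/−4.0/−2.5.
- −2/−6/−6: d = 4, line −2.67/−4.67/−6.67.
- 0/−6/−6: d = 6, line −1/−4/−7.

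**How often BIC picks the line.** Simulation used maximum likelihood with a random person intercept, 2,000 runs per setting. The means are after selection, so they include the runs where BIC kept categorical visits.

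| True effect | ρ | Line chosen | Mean after selection |
|---|---|---|---|
| −6/−3/−3 | 0.4 | 98.5% | −5.58/−3.95/−2.46 |
| −6/−3/−3 | 0.6 | 96.8% | −5.56/−3.93/−2.57 |
| −2/−6/−6 | 0.4 | 97.1% | −2.65/−4.80/−6.66 |
| −2/−6/−6 | 0.6 | 93.7% | −2.57/−4.82/−6.57 |
| 0/−6/−6 | 0.4 | 89.1% | −0.77/−4.33/−6.80 |
| 0/−6/−6 | 0.6 | 76.0% | −0.58/−4.65/−6.61 |

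Set against the visit-specific estimates from the same runs, the bias is about 0.4–0.8 points at months 2 and 6 and 0.9–1.6 at month 4. The visit-specific model stayed unbiased throughout. For −6/−6/−6 and −2/−4/−6, BIC picked the line in at least 99.8% of runs, without bias.

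**Closed-form check.** The line is kept when a 2-df chi-square statistic falls below 2 ln N. With a flat control arm its non-centrality is d²/(6 × 196 × (1 − ρ)/96). For d = 6 and ρ = 0.6 this is 36/4.9 = 7.35. With N = 576 rows (192 × 3), 2 ln N = 12.71 and the probability is 0.755, in line with the simulated 76.0%. If BIC counts 192 people instead, 2 ln N = 10.51 and the probability is 0.64. Across the six settings, counting people gives 64–97%. The protocol does not say which N applies.

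**Fallback to a plain linear model on three visits.** Simulated under the null, 2,500 runs per setting, without person or group effects, over the plan's ICC range and ρ of 0.4–0.7:

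- Visit-specific 6-month effect: model SE about 2.01–2.02 against a true 2.02–2.09; type I error 4.8–5.9%.
- Arm-by-time slope, per visit interval: model SE 1.42–1.43 against a true 0.76–1.11; type I error 0–2%. In formula, the model SE is √(196/96) = 1.43 and the true SE is √(196(1 − ρ)/96), which is 1.11 at ρ = 0.4 and 0.90 at ρ = 0.6. The ratio 1/√(1 − ρ) is 1.29 and 1.58.

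Neither estimate is biased by the fallback itself.

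**The case against.** Much of the case on the other side stands. The BIC rule and the convergence trigger are both stated in advance. A reader might infer that an unblinded analysis team can swap models at will, but minimum BIC leaves it no choice, and discretion enters only through the open wording of the fallback. Prespecification does not cure the conflict, though, because the rule itself leads away from the stated target.

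A reader might also infer that the fallback makes the secondary standard errors badly wrong. For the visit-specific effects the plan names, it does not, at the plan's ICC. Type I error of 14–19% (ρ = 0.4–0.6) would apply to a single effect averaged over visits, which the plan never proposes. Nor does the protocol say the person effect is dropped. The sentence names only group effects and directly follows the trauma model, which has one follow-up and so no within-person correlation to lose.

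It is tempting to say that fixed group effects would be collinear with arm. That holds only if a group is an M-Body class. Study design and Sample size speak of cohorts or blocks containing both arms, while Primary and Secondary outcome analyses lean towards treatment groups, so the text does not settle it. Nor does a class variance estimated at zero, which is likely at this ICC, show that the fallback would be used: a zero estimate is not necessarily a convergence failure.

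Finally, biases of 2.7 points at month 4 and 1.3 at months 2 and 6 require a 4-point departure from linearity, two-thirds of the meaningful difference. Nothing in the protocol suggests that shape. The biases found here are below the visit-specific SE of about 2 points.

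**Conclusion.** The conflict over BIC holds. The section promises visit-specific effects and adopts a rule that would usually remove them, including under moderately non-linear effects. The bias is about 0.4–0.8 points at months 2 and 6 and 0.9–1.6 at month 4 (roughly 0.03–0.06 and 0.06–0.11 of the SD of 14). It is nil if the effect is constant or linear in time. These figures rest on the assumed correlation and effect shapes, complete data and BIC counted over rows.

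The fallback point holds only conditionally. If applied to the three-visit outcomes, it leaves out a correlation the section calls necessary. The harm is then mainly to an arm-by-time slope, which is where the BIC switch leads; its SE would be 29–58% too large at ρ = 0.4–0.6, so real differences in trend could be missed.

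Severity is minor: the analyses are exploratory and the primary analysis is untouched.

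**What to change.** Report the model with categorical visit and arm-by-visit terms as the secondary analysis for IDS-C, GAD-7 and anger. Drop the BIC switch and show the linear growth model as supportive only.

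State that any convergence fallback for these repeated outcomes simplifies the group effect first and always keeps person-level correlation, through a random intercept or person-clustered standard errors. Say whether the sentence also covers trauma. Define group, and allow fixed group effects only if a group is a randomisation cohort containing both arms.

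This takes a few sentences in the analysis plan. The statistical cost is two more parameters per model.
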